**Methods and analysis:**

Children with (n=300) and without HIV (n=300), aged 8–16 years, established on ART, will be recruited into a frequency-matched prospective cohort study and compared. Musculoskeletal assessments including dual-energy X-ray absorptiometry, peripheral quantitative computed tomography, grip strength and standing long jump will be conducted at baseline and after 1 year. Linear regression will be used to estimate mean size-adjusted bone density and Z-scores by HIV status (ie, total-body less-head bone mineral content for lean mass adjusted for height and lumbar spine bone mineral apparent density. The prevalence of low size-adjusted BMD (ie, Z-scores <−2) will also be determined.

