**Figure 1 F1:**
[figure not shown]
Hypothesised changes in bone mass across the life course in HIV-infected and HIV-uninfected individuals.

The mechanisms by which HIV may lead to low size-adjusted BMD in children are not fully understood but are likely multifactorial, including HIV-associated factors (eg, ART drugs, HIV disease stage) and traditional risk factors (eg, hypogonadism, smoking, alcohol, low physical activity and vitamin D deficiency).^15^ HIV infection promotes systemic immune activation and production of inflammatory cytokines (eg, tumour necrosis factor α), which, in turn, promote increased bone resorption.^16^ ART initiation, particularly with tenofovir (part of the first-line ART regimen in SSA), predicts an initial decline in BMD which stabilises after 2 years in adults.^17^ It is thought that tenofovir may cause renal proximal tubule toxicity, resulting in phosphate wasting and increased bone turnover.^18^ Although tenofovir and protease inhibitors have been associated with low BMD in adults,^19 20^ studies in children have shown inconsistent findings.^21–23^ Malnutrition, opportunistic infections and social deprivation may also impede musculoskeletal development. Reduced physical activity, associated with HIV,^24^ may also impair muscle development and limit impact loading to reduce osteocyte-mediated bone accrual.^25 26^ In adults, weak grip strength has been associated with increased falls and fracture risk.^27^ Although muscle (lean) mass has also been shown to predict the magnitude of bone accrual during growth,^28^ few studies have compared muscle strength and function between children with and without HIV. Interestingly, a small Canadian study showed deficits in muscle power in CWH.^29^

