### Study design

CWH aged 8–16 years and established on ART (n=300) and a comparison group of children without HIV, frequency-matched for age and sex (n=300) will be recruited into a prospective cohort study. Detailed musculoskeletal assessments will be conducted at baseline and after 1 year.

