Baseline mean TBLH BMC^LBM^ and LS BMAD Z-scores and the prevalence of low TBLH BMC^LBM^ and LS BMAD Z-score will be compared between CWH and without HIV. Among CWH, the association between a priori defined risk factors (ART duration, ART type, proportion of life on treatment, age at ART initiation, CD4 count, viral load, bone age, pubertal stage, nutrition, socioeconomic status and orphanhood) against size-adjusted BMD will be examined using multivariable linear regression (Z-score as a continuous variable) and multivariable logistic regression (as defined by the Z-score cut-off of <−2). Successful antiretroviral therapy will be defined as a viral load of less than 1000 copies/mL. Paired sample t-test or non-parametric Wilcoxon test will be used to assess for differences in TBLH BMC and LS BMAD on children with and without HIV between baseline and follow-up. Multivariable linear regression will be used to analyse the mean percentage change in TBLH BMC^LBM^ (g) and LS BMAD (g/cm^3^) between children with and without HIV. Models will be adjusted for physical activity, calcium and vitamin D intake. Interaction between the effects of pubertal stage (bone age) and HIV on change in TBLH BMC^LBM^ and LS BMAD will be investigated to see if differences in bone density become more or less pronounced through puberty, that is, whether catch-up growth is possible, see figure 2. The regression coefficient (β) for percentage change in size-adjusted bone mass may suggest either no growth impairment (figure 2A), delayed puberty while maintaining the same growth trajectory (figure 2B) or delayed puberty with a reduced growth trajectory (figure 2C) in CWH. If β is markedly more positive in CWH, this suggests that catch-up growth may be possible (figure 2D). Pubertal delay in this study will be defined as the lack of the initial signs of puberty (Tanner stage 2) at an age that is more than 2 SD beyond the population mean^51^ and as chronological age minus bone age >2 years.^52^ Data for total body and lumbar spine DXA, tibial pQCT, hand grip strength and standing long jump in CWH will be analysed with reference to the comparator group of children without HIV.

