## Discussion

Although the scale-up of prevention of mother-to-child transmission has reduced perinatal HIV transmission, coverage is still not universal in most parts of SSA and therefore perinatal HIV infection is expected to affect large numbers of children for years to come. Furthermore, the scale-up of ART has reduced HIV-associated mortality dramatically so that CWH, who would previously have died in infancy or early childhood, are now reaching adolescence in increasing numbers. It is therefore important to understand the impact of HIV infection and its treatment on skeletal development during the critical period of puberty.

This study will determine the prevalence of low size-adjusted BMD in children with and without HIV in Zimbabwe, a country with a severe sustained early onset HIV epidemic. In addition, this study will determine risk factors for low size-adjusted BMD in CWH. We aim to identify factors amenable to intervention, which may be modifiable to maximise future bone health and minimise subsequent adult osteoporotic fracture risk. For example, reduced muscle function predicting low size-adjusted BMD may suggest targeted physiotherapy would be of benefit, which would warrant formal investigation.

Our study will provide insights regarding the mechanisms through which perinatal HIV infection affects the timing of pubertal onset and bone mass accrual. By measuring bone and muscle parameters at baseline and 1 year and by employing ‘gold standard’ size-adjustment methodology for DXA-measured BMD in the growing skeleton, this study will also provide insights into whether catch-up growth in terms of bone mass accrual is possible in HIV despite pubertal delay and provide age-related growth velocity data for CWH, with and without puberty.

While the age range in this study will allow analysis of pubertal delay in CWH, the follow-up period is insufficient to determine the impact on attainment of PBM, which probably occurs in the early 20s.^8^ In addition, this study is not sufficiently powered to analyse the effect of individual ART types on size-adjusted bone density. An additional limitation is the inability to obtain accurate height data for CWH prior to enrolment to fully study growth recovery. This is problematic given the significant role of poverty and nutrition, independent of HIV status, in the first 1000 days of childhood^53^; this may explain some of the deficit in final height attained by CWH.

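### The one-year change models adjust for physical activity, a possible HIV pathway, while their stated covariates leave out age, sex and socioeconomic status

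*Protocol article*

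**What the plan says.** All references are to the Protocol article.

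- **One-year change (Statistical analysis).** The between-group model is introduced as "Multivariable linear regression will be used to analyse the mean percentage change in TBLH BMC" and its lumbar spine counterpart. The next sentence gives the covariates: "Models will be adjusted for physical activity, calcium and vitamin D intake". An interaction between HIV and pubertal stage (bone age) on change follows, and is used to judge catch-up growth. Outcome measures lists percentage change as secondary.
- **Baseline comparison.** The baseline Z-scores and prevalences "will be compared between CWH and without HIV. Among CWH, the association between a priori defined risk factors", so the text passes to the models within children with HIV without naming covariates for the comparison. The Abstract says "Linear regression will be used to estimate mean size-adjusted bone density and Z-scores by HIV status", again without covariates.
- **Physical activity (Introduction, after Figure 1).** "Reduced physical activity, associated with HIV", it says, "may also impair muscle development and limit impact loading to reduce osteocyte-mediated bone accrual".
- **Matching.** Study design describes "a comparison group of children without HIV, frequency-matched for age and sex". The recruitment sections set the same quotas in both groups: 50 boys and 50 girls in each of three age strata.
- **Socioeconomic status.** It is on the list of risk factors examined within children with HIV. The Discussion refers to the "significant role of poverty and nutrition, independent of HIV status" in early childhood.
- **Aim (Study objectives).** The aim is the impact of HIV on size-adjusted bone density. No aim is stated for an effect of HIV that excludes activity.

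**The concern.** Both links of a pathway from HIV through physical activity to bone are in the protocol's own text. If HIV lowers activity and lower activity reduces accrual, holding activity fixed removes that part of the HIV effect. The coefficient then answers a narrower question than the stated aim.

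The covariate list also leaves out age and sex. The outcome is percentage change in unstandardised units (g and g/cm³) in children aged 8–16, so age and sex may well account for a good part of its variance. Socioeconomic status is also absent, although the groups come from different sources (hospital HIV clinics and government schools) and the protocol says social deprivation may impede musculoskeletal development.

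At stake are what the one-year HIV coefficient means, how precise it is, and how the interaction with pubertal stage can be read.

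**Working it through.** The protocol gives no effect size, SD or explained variance for one-year percentage change, so there is no planned figure to reproduce. The sample-size inputs concern baseline Z-scores and are not used. The sizes below are assumptions, in outcome SD units.

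**1. Adjusting for activity.** In a linear model without an HIV-by-activity interaction:

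adjusted effect = total effect − (HIV difference in activity × slope of outcome on activity)

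Assume a total effect of −0.23 SD and a slope of 0.2 SD per SD of activity.

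| HIV difference in activity | Product | Adjusted effect | Share removed |
|---|---|---|---|
| 0 | 0 | −0.23 | 0% |
| −0.3 SD | −0.06 | −0.17 | 0.06/0.23 = 26% |
| −0.5 SD | −0.10 | −0.13 | 0.10/0.23 = 43% |

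A simulation of 300 v 300 children balanced over six age-sex cells (1000 replicates) gave −0.228, −0.170 and −0.129 for the activity-adjusted effect. The shift depends entirely on whether activity differs by HIV status, and the protocol gives no size for that.

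**2. Omitting socioeconomic status.** Assume activity is 0.3 SD lower in children with HIV (slope 0.2), as in the second row. If socioeconomic status is also 0.3 SD lower, with slope 0.2, leaving it out adds 0.3 × 0.2 = 0.06:

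- No adjustment: −0.23 − 0.06 = −0.29.
- Activity adjusted, socioeconomic status omitted: −0.29 + 0.06 = −0.23, the assumed total effect.

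Here the two errors cancel. With other inputs the net error could go either way, so neither its direction nor its size follows from the document.

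**3. Omitting age and sex.** Equal quotas balance age stratum and sex at enrolment, so a linear mean difference is not confounded by them. What is lost is precision. With R² the share of outcome variance explained by age and sex, the standard error changes by the factor √(1 − R²), and the equivalent unadjusted group size is 300/(1 − R²).

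| Assumed R² | Factor | Fall in SE | Equivalent group size |
|---|---|---|---|
| 0.20 | √0.80 = 0.894 | 11% | 300/0.80 = 375 |
| 0.30 | √0.70 = 0.837 | 16% | 300/0.70 = 429 |
| 0.40 | √0.60 = 0.775 | 23% | 300/0.60 = 500 |

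In the simulation at R² = 0.20, adding the age-sex cells to a model with socioeconomic status took the standard error from 0.080 to 0.071, a fall of 0.009/0.080 = 11%.

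**4. The interaction with pubertal stage.** The quotas balance age overall, not within stage. The Introduction puts pubertal onset about a year later in children with HIV. At a given stage or bone age, those children will therefore tend to be older than their comparators. Without age in the model, stage-specific HIV contrasts can mix HIV with age. This is a qualitative argument; the document gives no figures to size it.

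**The case against.** - **Scope.** The covariate sentence belongs to a secondary analysis. A reader might infer that the primary baseline comparison is wrongly adjusted, or wrongly unadjusted. The document supports neither reading: the sentence follows the one-year model, and a condensed article's silence on baseline covariates is no fault. This objection stands, and the point is limited accordingly.
- **Bias.** A reader might conclude that the one-year estimate is biased, towards zero in particular. That needs group differences in activity or socioeconomic status that the document does not quantify, and the two effects can cancel. So the conclusion is only that the coefficient may not be the total effect.
- **Power.** It is tempting to turn the mediated share into lost power using the sample-size section. Those inputs are for baseline Z-scores, so the calculation would not describe this model.
- **Age and sex.** Equal quotas do remove confounding of the overall contrast at enrolment, and pubertal stage in the interaction model will probably absorb some age-related variance. That reduces the gain but does not remove it, and it leaves age unbalanced within stage. Differential loss by one year could also disturb the balance.
- **Socioeconomic status.** The Discussion passage concerns early childhood and final height, and the comparison schools lie in the same catchment area. A group difference is plausible, not shown. Calcium and vitamin D intake may also capture some deprivation, so they could act as confounders; the argument for moving them out of the main model is weaker than for activity.
- **Condensed article.** The list is not said to be exhaustive. Even so, adjusting for activity is stated outright, and no aim in the article calls for an effect net of activity.

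**Conclusion.** The point holds for the one-year percentage-change models only. As stated, they condition on a variable the protocol itself describes as related to HIV and to bone accrual, so the coefficient may differ from the overall impact of HIV by an amount the document cannot supply. Omitting age and sex mainly loses precision: about 11–23% on the standard error if they explain 20–40% of the variance, which is an assumption. It also leaves age possibly unbalanced within pubertal stage in the interaction analysis. Socioeconomic status is a possible confounder of unknown size and direction. This is an inexpensive improvement to a secondary analysis.

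**What to change.** For the one-year change outcomes:

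1. Make the main model HIV status adjusted for age, sex and socioeconomic status, the last defined as for the models within children with HIV.
2. Report the model that adds physical activity, calcium and vitamin D intake as secondary and explanatory, described as the HIV difference with those factors held fixed.
3. Base the conclusion about the overall impact of HIV on the main model.
4. Include age in the HIV by pubertal stage interaction model.

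The cost is one extra model per outcome and a change of wording. Age, sex, activity and diet are already planned for collection in both groups. Socioeconomic status is already a planned risk factor and sociodemographic details are in the questionnaire, but the article does not name the measure, so the team should confirm that it is available for both groups.

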**Figure 2 F2:**
[figure not shown]
Hypothesised growth scenarios to be assessed as interactions between pubertal stage and HIV status on change in bone mass.

For the purposes of normative data derivation, children without HIV who have any diagnosis or evidence of muscle or bone disease will be excluded. Then outliers with bone density, hand grip strength or standing long jump data beyond 2 SD from the mean will have their case record reviewed to exclude cases with underlying bone or muscle pathology. The remaining population will be used to generate normative references ranges for these quantitative traits.

### Data management

Data collection, management and storage will be governed by standard operating procedures and will follow the principles of Good Clinical Practice (GCP). Data will be captured using hand-held tablets for the questionnaires. Paper forms will be available in case of failure of electronic data entry. Microsoft Access will be used as the main back-end database as it allows programming of quality control checks and conditional data validation. GCP compliant audit trail modules will be incorporated into the databases and reports of aggregated data will be reviewed on a monthly basis. In order to assure data quality and consistency, all staff will receive regular training and regular quality checks will be conducted. Paper records will be stored for 8 years after the completion of research in secure, locked storage facilities. Field staff will download data to the central database, which is backed up onto an encrypted external hard drive daily, and to additional off-site and secure cloud back-up. The off-site back-up copies will be stored through the London School of Hygiene and Tropical Medicine (LSHTM) Research Data Management Support Service that has an established data repository. In order to preserve the long-term value of these data, it will be stored backed-up here indefinitely. Anonymised research data will be made available for sharing through the open access data repository established by the LSHTM Data Management Support Service at the time of publication. This will allow other research groups to request access to study data and tools. Information on other researchers’ data will be included in every study publication.

### Patient and public involvement

While patients were not directly involved in the design and conduct of the study, feedback from patient experiences in the study will be used to inform planned public engagement activities, which include science fairs, conducted by the research team at schools from where participants were recruited.

### Study status

Recruitment to this study began in May 2018 and is planned until August 2019. Study follow-up will run from May 2019 to August 2020.

## Discussion

Although the scale-up of prevention of mother-to-child transmission has reduced perinatal HIV transmission, coverage is still not universal in most parts of SSA and therefore perinatal HIV infection is expected to affect large numbers of children for years to come. Furthermore, the scale-up of ART has reduced HIV-associated mortality dramatically so that CWH, who would previously have died in infancy or early childhood, are now reaching adolescence in increasing numbers. It is therefore important to understand the impact of HIV infection and its treatment on skeletal development during the critical period of puberty.

This study will determine the prevalence of low size-adjusted BMD in children with and without HIV in Zimbabwe, a country with a severe sustained early onset HIV epidemic. In addition, this study will determine risk factors for low size-adjusted BMD in CWH. We aim to identify factors amenable to intervention, which may be modifiable to maximise future bone health and minimise subsequent adult osteoporotic fracture risk. For example, reduced muscle function predicting low size-adjusted BMD may suggest targeted physiotherapy would be of benefit, which would warrant formal investigation.

Our study will provide insights regarding the mechanisms through which perinatal HIV infection affects the timing of pubertal onset and bone mass accrual. By measuring bone and muscle parameters at baseline and 1 year and by employing ‘gold standard’ size-adjustment methodology for DXA-measured BMD in the growing skeleton, this study will also provide insights into whether catch-up growth in terms of bone mass accrual is possible in HIV despite pubertal delay and provide age-related growth velocity data for CWH, with and without puberty.

While the age range in this study will allow analysis of pubertal delay in CWH, the follow-up period is insufficient to determine the impact on attainment of PBM, which probably occurs in the early 20s.^8^ In addition, this study is not sufficiently powered to analyse the effect of individual ART types on size-adjusted bone density. An additional limitation is the inability to obtain accurate height data for CWH prior to enrolment to fully study growth recovery. This is problematic given the significant role of poverty and nutrition, independent of HIV status, in the first 1000 days of childhood^53^; this may explain some of the deficit in final height attained by CWH.

The bone architecture measured by pQCT in this study will provide separate assessments of trabecular and cortical bone density, and bone geometry and strength in Zimbabwean children. The evidence from studies in adult men established on ART demonstrates impairments in trabecular and cortical bone architecture.^54^ Whether the same applies to children needs to be determined.

Furthermore, we will establish novel comparator data for DXA, pQCT, bone age, hand grip strength and standing long jump for a Zimbabwean population, which will be used for future research in this context. Although this represents the first steps towards developing normative reference data, the extent to which the children without HIV infection in this study are representative of the Zimbabwean population of 8–16 year olds is unknown. Furthermore, this study will establish a biorepository for future research, for example, potential bone turnover marker measurement and genotyping.

Given the magnitude of the HIV epidemic in SSA and the large cohort of young people who may experience impaired bone accrual, musculoskeletal disability or fracture as they reach adolescence and early adulthood, it is imperative to characterise the impact of perinatal HIV on musculoskeletal development.

## Ethics and dissemination

Ethical approval has been granted by the LSHTM Ethics Committee (Ref: 15333; 14 May 2018), the Institutional Review Board of the Biomedical Research and Training Institute (Ref: AP 145/2018; 20 February 2018), the Joint Research Ethics Committee for University of Zimbabwe College of Health Sciences and the Parirenyatwa Group of Hospitals (JREC) (Ref: 11/18; 1 March 2018), Harare Central Hospital Ethics Committee (HCHEC) (Ref: 170118/04; 23 February 2018), the Medical Research Council of Zimbabwe (Ref: MRCZ/A/2297; 10 April 2018) and the Ministry of Primary and Secondary Education Zimbabwe (Ref: C/426/Harare; 13 February 2018). This study is registered with the ISRCTN registry (Ref: ISRCTN12266984).

Study progress will be reported annually to MRCZ. Results of interim data analysis will be presented at national and international research meetings and conferences. Study findings will be published in international peer-reviewed scientific journals and disseminated to research communities at the end of study.
